#### Recruitment of Patients

Participating practices are asked to search their electronic records to identify a list of 160 patients who meet the selection criteria (Table 2). Previous research suggests that 25% of these will be eligible and willing to participate. The rationale for the eligibility criteria is to recruit sufficient patients with high to moderate risk of cardiovascular disease or diabetes to participate in the full intervention (both in general practice and the referral program). Patients in the 40-55 age groups are targeted by existing health checks but are less likely to have multiple risk factors or to be at high CVD or diabetes risk. Thus in this age group we are specifically targeting those who already have physiological risk factors. Patients aged 56-64 are more likely to have multiple risk factors and also to be at increased risk because of their age. The majority of general practice patients older than 64 years have already developed a chronic disease.

**Table 2 T2:** Patient selection criteria

Inclusion criteria	
• Aged 40-55 with hypertension and/or hyperlipidaemia	
• Aged 56-64	
• Attended the practice in the last 12 months	

**Exclusion criteria by practice**	**Exclusion criteria by GP**

Diagnosed or treated for:	• Has current severe illness or personal circumstances which are of overriding concern;
• Diabetes	
• Cardiovascular disease	• Is deceased (up to date medical records generally prevent this)
• Renal disease	• Is no longer a patient of the practice;
• Stroke	• Is unable to speak adequate English;
	• Has diabetes or cardiovascular disease;
	• Is unlikely to be able to read and understand the information sheet and consent form because of significant cognitive impairment (e.g. dementia.)

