• have history of gestational diabetes (GDM)
• have 'Pre diabetes' - (impaired glucose tolerance or impaired fasting glycaemia)
• have elevated blood pressure (BP ≥ 140/90 on two occasions) or on treatment for high blood pressure
• have high Lipid: Total Cholesterol (TC) > 4.5 mmol/L or Low Density Lipoprotein (LDL) > 2.5 mmol/L or Triglyceride (TG) > 2.0 mmol/L or on treatment for it
• are overweight: BMI > 28 or waist circumference > 102 cm in males and 88 cm in females
• currently smoke.

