#### Sample size calculation

All sample size calculations use a significance level of 5% and power of 80%, with design effects and estimated expected differences between the intervention and control groups based on previous research

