##### Reduction in physiological risk factors

Assuming a design effect due to clustering of 1.8, loss to follow up of 20% and standard deviations based on data from general practice diabetes registers [34]:

• weight: assuming a standard deviation of 19, a sample size of 382 will be sufficient to detect a mean difference of 4 Kg in weight between intervention and control groups.

• LDL cholesterol: assuming a standard deviation of 0.9, a sample size of 342 will be sufficient to detect a mean difference of 0.2 mmol/L in LDL-cholesterol between intervention and control groups.

• blood pressure: assuming a standard deviation of 11, a sample size of 228 will be sufficient to detect a mean difference of 3 mmHg in systolic blood pressure between intervention and control groups.

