##### Reduction in behavioural risk factors

Assuming a design effect due to clustering of 1.8 and a 20% loss to follow up with estimates based on previous research [35]:

• if patients eat a standard deviation 2.1 portions of fruit and vegetables a sample of 288 in each group would have sufficient power to detect a mean 0.5 portion difference.

• if 22% smoke, a sample of 363 in each group would have sufficient power to detect a 6% difference.

• if 30% consume alcohol at risk levels, a sample of 362 in each group would have sufficient power to detect a 7% difference.

• For physical activity, a score of 2.1 in a sample of 305 in each group would have sufficient power to detect a mean 0.5 score difference.

We aim to recruit 30 general practices and identify 160 patients from each practice (total = 4800). From this we anticipate 25% responses in each group (600 patients in each group). An estimated 20% loss to follow-up will leave 480 patients in each group, of which we estimate 60% are high risk (288 patients in each group) (Figure 3).

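### The number of high-risk patients expected for primary hypothesis 3 narrowly misses two or three of the stated sizes, rests on an unexplained 60% share, and gives about 28% to 68% power on the plan's own inputs rather than 80%

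*Protocol article*

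**What the plan says.** Table 1 of the protocol article words primary hypothesis 3 as a 12-month comparison of behavioural and physiological risk factors between high-risk patients in the two groups.

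The section on sample size calculation sets common terms ("All sample size calculations use a significance level of 5% and power of 80" per cent). For both the physiological and the behavioural outcomes it then assumes a design effect of 1.8 and 20% loss to follow-up. The stated sizes are:

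- **Physiological:** weight, "a sample size of 382 will be sufficient to detect a mean difference of 4 Kg"; LDL 342; systolic pressure 228. None of the three is labelled as per group or total.
- **Behavioural, all per group:** fruit and vegetables 288; smoking, "a sample of 363 in each group would have sufficient power to detect a 6% difference"; alcohol, "a sample of 362 in each group would have sufficient power to detect a 7% difference"; physical activity, "a sample of 305 in each group would have sufficient power".

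The section ends with the recruitment projection: 4800 patients identified, 25% responding (600 per group), and 20% loss, which "will leave 480 patients in each group, of which we estimate 60% are high risk (288 patients in each group").

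Two tables bear on the 60%. Table 2 admits younger patients only if "Aged 40-55 with hypertension and/or hyperlipidaemia", and those aged 56-64 on age alone. Table 6 makes a patient high risk on any one factor. Among these are treated or raised blood pressure, BMI above 28, current smoking, and lipids ("have high Lipid: Total Cholesterol (TC) > 4.5 mmol/L", or the LDL or triglyceride limits, or treatment).

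**The concern.** The section lists the sizes needed at 80% power and closes with a projected number, but never sets one against the other. It does not say whether the projection covers each outcome, whether each size counts patients before or after loss, or, for the physiological outcomes, whether it is per group or total.

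The projection also depends on a 60% high-risk share for which no basis is given and which sits uneasily with the entry criteria. That share fixes the analysable number for hypothesis 3, the expected referral load, and the size of the low-risk group that the Discussion says the study also examines.

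At stake is how results are read. A null finding on smoking or alcohol would be judged against a claimed 80% power that the expected numbers may not deliver.

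**Working it through.** **1. The projection.** 30 x 160 = 4800; x 0.25 = 1200, or 600 per group; x 0.8 = 480; x 0.6 = 288. The stated figure reproduces exactly. High-risk patients enrolled, before loss: 600 x 0.6 = 360 per group.

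**2. Is loss already inside the stated sizes?** The text says so. The arithmetic agrees for the physiological outcomes: (1.960 + 0.842)² x (SD/difference)² x 1.8 x 1.2, with (1.960 + 0.842)² = 7.849, gives

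- weight (SD 19, difference 4): 382.5, stated 382
- LDL (0.9, 0.2): 343.3, stated 342
- systolic pressure (11, 3): 227.9, stated 228

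The same form with SD 2.1 and difference 0.5 gives 299, against the stated 288 (diet) and 305 (activity, reading its 2.1 as an SD). The form contains an allowance for loss (x 1.2). It lacks the factor 2 that a comparison of two means needs per group. The standard two-group formula with the same inputs does not reproduce the stated sizes.

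**3. Like-for-like comparison, sizes including loss against 360 enrolled.**

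| Outcome | Stated size | Against 360 |
|---|---|---|
| Weight | 382 (unit not stated) | short by 22 if per group |
| Smoking | 363 | short by 3 |
| Alcohol | 362 | short by 2 |
| LDL | 342 (unit not stated) | met |
| Physical activity | 305 | met |
| Fruit and vegetables | 288 | met |
| Systolic pressure | 228 (unit not stated) | met |

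The share that would meet every stated size is 382/600 = 63.7%.

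**4. The 60% share.** Suppose every entrant aged 40-55 is high risk and they form a fraction f of the sample (assumption; the article does not give f). Then 60% overall requires a proportion (0.6 - f)/(1 - f) of those aged 56-64 to be high risk: 50% at f = 0.2, 43% at 0.3, 33% at 0.4, 20% at 0.5, and 0% at 0.6. At f = 0.5 the required 20% is below the 22% smoking prevalence that the sample size section assumes, before lipids, blood pressure, BMI or waist are counted.

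**5. Power at the expected number.** Two-sided 5%, design effect 1.8, no credit for baseline adjustment. Effective number per group: 288/1.8 = 160. Power = Φ(difference/SE - 1.96), with SE = SD x √(2/160) for means and √[(p1(1-p1) + p2(1-p2))/160] for proportions. Smoking is taken as 22% against 16%, alcohol as 30% against 23%. The last column repeats this with 480/1.8 = 266.7, as if every patient followed up were high risk.

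| Outcome | SE at 288 | Difference/SE | Power at 288 | Power at 480 |
|---|---|---|---|---|
| Weight | 2.124 | 1.883 | 47% | 68% |
| LDL | 0.1006 | 1.988 | 51% | 73% |
| Systolic pressure | 1.230 | 2.439 | 68% | 88% |
| Fruit and vegetables | 0.2348 | 2.130 | 57% | 79% |
| Smoking | 0.0437 | 1.372 | 28% | 43% |
| Alcohol | 0.0492 | 1.423 | 30% | 45% |

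Physical activity equals the diet row if its 2.1 is an SD. A pooled-variance test changes the smoking and alcohol figures by less than one percentage point.

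**6. What baseline adjustment could recover.** Before loss, weight needs 2 x 7.849 x (19/4)² x 1.8 = 638 per group. If adjustment multiplies this by (1 - r²), with r the baseline to 12-month correlation and the design effect held at 1.8, then 288 suffices when 1 - r² = 288/638, so r is about 0.74.

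**The case against.** A reader might set 288 directly against the stated sizes and conclude that five outcomes fall short. That takes the 20% loss off twice, because 288 is after loss and the sizes already allow for it. Against 360 enrolled, LDL and physical activity are met. The smoking and alcohol gaps are trivial: taking the stated sizes at face value, 360 in place of 363 leaves power at about 79.7%. Even for weight, 360 in place of 382 leaves about 78%. Weight counts as a miss only if 382 is per group. As a total it would be 191 per group and easily met, although the formula that reproduces 382 does not support a total either.

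A reader might also infer that Tables 2 and 6 contradict the 60%. They do not strictly do so. It is offered as an estimate, and neither the age mix nor the frequency of Table 6 factors at 56-64 is given. Only more than 60% of entrants aged 40-55, all of them high risk, would make it impossible. An underestimate would also err on the safe side, since a share near 64% meets every stated size. The first two parts of the point therefore partly offset each other.

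Nor does the article anywhere claim that all the sizes are met.

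These objections stand, and they limit the shortfall and the share to matters of clarification. They do not answer the power calculation. A higher share moves the number towards 480, where only systolic pressure clears 80%. Baseline adjustment is planned and could recover much for the continuous outcomes, but the sample size section credits none.

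**Conclusion.** The point holds, in three parts of unequal weight.

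- **Stated sizes against the projection:** smoking and alcohol are missed by 3 and 2 patients per group and weight by 22 if 382 is per group; the other four are met. This is small.
- **The 60% share:** it looks too low for these entry criteria and this broad definition. That is tension rather than proof, because the age mix is unknown.
- **Power:** the stated 80% is not supported. On the plan's own inputs it is about 28% to 68% at 288 followed up per group, and about 43% to 88% even at 480.

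The power figures assume a two-sided test (sidedness is not stated), a design effect of 1.8, reductions from the stated prevalences, and no gain from baseline adjustment. Such a gain could change the conclusion for the continuous outcomes. The section needs correction as written.

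**What to change.** 1. Beside each stated size, say whether it is per group or total, and before or after loss.
2. Re-derive the high-risk share by applying Table 6 to the expected age mix, or to the baseline data collected before randomisation, and restate the expected high-risk numbers enrolled and followed up per group.
3. Add a small table giving, for each outcome, the power or the detectable difference at that number from a two-group formula. If a gain from baseline adjustment is claimed, state the assumed correlation and its source.

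The cost is some rewording and one table. No extra recruitment is needed. Some stated figures will become less favourable, most clearly for smoking and alcohol.

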**Figure 3 F3:**
[figure not shown]
**Predicted patient recruitment**.

### Data Analysis

#### Quantitative evaluation - statistical analysis

Quantitative data analysis will be conducted using SPSS and ML-Win (Multilevel statistics for Windows). Multilevel linear models will be used for continuous response variables and multilevel logistic models for binary responses. Co-variates will be included in the analyses to adjust for baseline differences between the intervention and control groups.

The analysis will include changes in the study variables before and after the intervention in both intervention and control groups, including changes in patients' lifestyle risk factors and comparison of outcomes at 12 months between the intervention and control groups after adjusting for baseline differences.

#### Qualitative evaluation

As this is a complex intervention delivered within the context of normal practice, a qualitative evaluation of the implementation process is important in interpreting the study findings [36]. Semi-structured interviews will be conducted with intervention GPs, PNs and IOs to explore their views on (a) the *CHANGE for HIPS *intervention program, (b) experiences of implementation (including feasibility, barriers and facilitators), (c) perceptions of patients' views/experiences of participation and (d) key lessons for dissemination of the program into routine service provision. All interviews will be transcribed verbatim and subject to thematic analysis using NVivo 8 [37] to identify convergence and divergence of themes.

### Pilot Study

All procedures and tools used in the study have been pilot tested with a practice in a nonparticipating DGP.

### Ethics

The project has been approved by the University of New South Wales Human Research Ethics Committee (HREC).

## Discussion

Much of the focus in general practice primary preventive care has been on assessment of risk, use of medications, and brief interventions to address single risk factors. While trials have demonstrated the effectiveness of intense interventions to prevent diabetes or cardiovascular disease, it has been difficult to replicate this within routine practice. This is one of the first studies in Australia to evaluate an intervention which includes assessment and brief intervention in routine general practice coupled with a more intensive referral-based intervention based in the local DGP. The trial is unique in that the intervention is delivered as part of routine practice (both in general practices and the DGP), and the study aims to examine its impact in both high and low risk patients. The study will also provide valuable qualitative data on the barriers and facilitators to implementing brief intervention and referral of high risk patients to more intensive intervention in the general practice setting.

The study involved a strong collaborative partnership with DGPs and non-government organizations such as the National Heart Foundation. These relationships are essential not only to recruit participants into the study but also to deliver an effective intervention and subsequently implement the findings.

The results of this study will help inform improvements to the implementation of primary prevention of vascular disease and inform the implementation of other preventive health initiatives which involve referral to group programs outside general practice, such as the 45-year-old health check and the diabetes risk assessment in Australian general practice. The findings of the study will be disseminated using peer-reviewed journals, conference presentations, and research summaries tailored for practitioners, service managers and policy makers. We anticipate that it will inform broader policies and strategies including:

• defining the optimal roles of general practice staff, allied health providers and group referral programs in providing interventions for low and high risk patients

• redesigning the pathways for referral and follow up of high risk patients

• providing more effective support for primary prevention through DGPs in general practice;

• redesigning the Medicare Benefits Schedule (MBS) preventive care related item numbers;

• integrating the complex preventive interventions required to prevent chronic diseases such as diabetes within routine general practice and its associated services and programs.
